#### II.Data preprocessing

All video files saved from the ultrasound (US) devices and the frames separated by the OB-GYN/Cardio (OBC) department into folders corresponding to the key planes are collected into the cloud. The Data Science / IT department (DSIT) will process the frames for obeying the anonymization regulations. This implies two essential aspects. One is obviously to erase the information that refers to the patients from the frame samples and the video files, as file and folder names. However, before deleting such information, unique strings will be assigned to each patient, such that, when separating the samples into sets for training, validating, and testing the model, all images that belong to the same patient will be placed in only one of the three sets. In the case that some samples from a patient would be placed in the training set and other samples from the same patient would be put in the validation (or test) set, the machine learning model would be biased since these samples would be more similar compared to those coming from different patients. Hence, before the anonymization takes place, unique codes will be generated for each patient in turn, and the code will appear on the names of the files.

Subsequently, the samples of the patients will be split into training, validation, and test sets, keeping the proportions of 60–20%-20%. These approximate proportions need to be kept for each class in turn. As mentioned above, images belonging to the same patient will be placed in the same set, be it training, validation or test. In addition, even if the samples come from a different video file but from the same patient, e.g., if the patient went to a consultation at another date, the samples will be placed in the same folder to avoid biasing the model.

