#### IV. Experiments

All the recent DL entries will be tailored and tested on the current scenario of key view identification. Their prediction results will be analyzed compared to the ground truth marked by the OBC. The metrics concern accuracy, precision, recall, and F1-score. A hierarchy will be built based on statistical testing, and the best algorithm will represent the AI module for this scenario. Different architectures can be tried. Some have a relatively small number of layers, and they are faster as concerns running time. Others are very deep, meaning that they have a high number of layers hence they take longer to train but are potentially more accurate. It is essential to be fast in the testing stage for the final trained model used in practice, as the training model would not be later re-initiated. Although the more complex models still run slower in the testing phase than those with fewer layers, the differences are minimal. However, the current task needs to be thoroughly tested since it might be the case that shallow models also lead to accurate results and, if this is the case, they will be preferred. The accuracy-speed equilibrium will be considered when ranking the approaches since the system will finally perform on a video.

Once a new video is available in practice, the model chosen for the task will highlight each key feature and the probability/certainty. Additionally, the final application will present a graphical and numerical report showing the number of frames with key planes identified and the indication of the certitude it has for them. Finally, the OBC physicians will validate all the intermediary findings at frame level and the meaningfulness of the video labeling.

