#### V. Sample size calculation

As opposed to classical statistics, for machine learning in general, but for deep learning tasks that involve image classification in particular, there is not a general pre hoc rule for calculating the sample size. The pre hoc model-based approaches rely on the features of the algorithms taken into consideration. We underline that the approaches to be used are non-linear, in fact they are from the deep learning family. The classification accuracy will continue to improve as more data is included in the training process, as opposed to standard machine learning algorithms, where the accuracy reaches a plateau when the data attains a certain threshold. The statistical heuristic methods often take into account the number of classes, the number of input features and the number of parameters of the model. However, considering that the number of parameters of a deep learning approach is usually of many millions and that for each distinct parameter there are usually tens of samples necessary, a statistical heuristic method becomes unusable. A rule of thumb in deep learning is to have 1000 samples per class, as used in the ImageNet dataset pioneered in the Large Scale Visual Recognition Challenge 2012. The number of samples is smaller than what a heuristic estimate would indicate, since transfer learning will also be employed and additionally the data set will be artificially enlarged via image augmentation. Accordingly, it is intended to have at least 6000 images (around 1000 per class) within our data set, which could be extracted from approximately 300 ultrasound video files. We intend to make a post hoc sampling estimation study by considering subsets of the data for training and observing the results on the same test set.

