### Statistical methods

There will be several deep learning architectures trained on the obtained data set. In order to select the most prolific one and be assured that its results are not based on chance, the performance of the different models tried in terms of the considered metrics will be assessed under random sub-sampling cross-validation with multiple repetitions and the significance in the difference of the results will be checked via a Wilcoxon signed-rank test.

The performance of the computational models on videos taken by inexperienced sonographers will be statistically assessed compared to the results on scans where an expert made the examination. In order to achieve this, two sets of video scans will be completed, one containing video files made by experienced sonographers and the other made by inexperienced ones. The frames that the computational model labels will be extracted from the scans, and the experienced physicians will validate their predictions for both types of data. A t-test and a Mann-Whitney test for independent test samples will be used for verifying the differences in the results on the two sets.

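### The comparison of model results by operator experience names two independent-sample tests but does not fix the unit of analysis, allow for clustering or say which test decides

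*Protocol article*

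**What the plan says.** The second paragraph of Statistical methods asks whether the model performs differently on scans by experienced and by inexperienced operators. The data are built in two steps: "two sets of video scans will be completed, one containing video files made by experienced sonographers and the other made by inexperienced ones"; then "The frames that the computational model labels will be extracted from the scans, and the experienced physicians will validate their predictions", for both kinds of scan. The analysis is one sentence: "A t-test and a Mann-Whitney test for independent test samples will be used for verifying the differences in the results" between these two sets.

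Other sections bear on it:

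- IV. Experiments lists the performance measures: "The metrics concern accuracy, precision, recall, and F1-score".
- II. Data preprocessing keeps all images of one patient in the same split because "these samples would be more similar compared to those coming from different patients".
- V. Sample size calculation plans for "at least 6000 images (around 1000 per class) within our data set, which could be extracted from approximately 300 ultrasound video files".

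For this comparison the article states no significance level, set sizes, number of operators, intraclass correlation or allowance for clustering.

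**The concern.** Both named tests require independent observations. The data arise as frames within 5-second sweeps, sweeps within patients, and sweeps within operators. Experience, the factor being compared, is a property of the operator. The article recognises within-patient similarity when it splits the data for training, but does not carry that principle into this comparison.

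If the correlation is ignored, the standard error of the difference is too small. The study could then report that the software works worse, or better, on inexperienced operators' scans when the gap only reflects variation between videos or operators. The system is meant to help early-stage sonographers, and this is the only test in the article of whether the model holds up on their scans.

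Naming two tests without a deciding rule adds a smaller problem. On right/wrong frame data the two are practically the same test, so the second adds nothing. On per-video summaries they can disagree, and nothing says which one counts.

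**Working it through.** The article gives no figure for this comparison, so there is none to reproduce. The check asks how far the type I error could move from an assumed two-sided nominal 5% under each reading of the unit.

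**Inputs**

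- Frames per video: m = 6000/300 = 20, from V. Sample size calculation. This is a planning figure for the whole image data set and only a proxy for the two comparison sets.
- ICC between frames of one video: not given; taken from 0.01 to 0.50.
- Videos per operator: not given; 5, 10 and 15 assumed.
- Operator ICC of per-video results: not given; 0.05 and 0.10 assumed.

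**Formulas** (large-sample)

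- Design effect: DE = 1 + (m − 1) × ICC, where m is the number of observations per cluster.
- Actual type I error of the unadjusted test: 2 × [1 − Φ(1.96/√DE)].

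**Reading 1: the frame is the observation (m = 20)**

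Example at ICC 0.05: DE = 1 + 19 × 0.05 = 1.95; 1.96/√1.95 = 1.40; error = 16.0%. The formula was checked with a beta-binomial simulation (assumed 30 videos per group, 20 frames each, 90% of frames correct, 2000 runs). The t-test and the Mann-Whitney test had identical rejection rates at every ICC.

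| ICC | DE | Error, formula | Error, simulation |
|---|---|---|---|
| 0 | 1.00 | 5.0% | 4.8% |
| 0.01 | 1.19 | 7.2% | 7.3% |
| 0.05 | 1.95 | 16.0% | 15.1% |
| 0.10 | 2.90 | 25.0% | 23.4% |
| 0.20 | 4.80 | 37.1% | 37.3% |
| 0.30 | 6.70 | 44.9% | 44.6% |
| 0.50 | 10.50 | 54.5% | 56.3% |

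At m = 20 the error reaches 10% at ICC 0.022 and 15% at ICC 0.045. The result depends on m: at ICC 0.10 it is 8.6% with 4 frames per video and 42.0% with 50.

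**Reading 2: a per-video summary is the observation**

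In the same simulation, tests on per-video accuracy rejected in 4.4% to 5.7% of runs at every frame-level ICC. Frame clustering is therefore harmless here, but that simulation contains no operator effect. With one, the same formula applies, now with m as videos per operator:

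| Videos per operator | Operator ICC 0.05 | Operator ICC 0.10 |
|---|---|---|
| 5 | DE 1.20, error 7.4% | DE 1.40, error 9.8% |
| 10 | DE 1.45, error 10.4% | DE 1.90, error 15.5% |
| 15 | DE 1.70, error 13.3% | DE 2.40, error 20.6% |

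These operator figures come from the formula alone and are approximate when operators are few.

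**The case against.** A reader might infer that frames go straight into the tests and that the type I error therefore is several times 5%. The documents do not support that:

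- The compared results belong to sets of videos. Validating frames is how the results are produced; it does not make each frame an observation.
- Precision, recall and F1 exist only after frames are aggregated, and the planned application reports frame counts and certainty for a video. Naming both a t-test and a Mann-Whitney test also fits per-video scores better than right/wrong frames.
- No level, ICC, set size or operator count is given. Across the assumptions above, the error runs from about 5% to over 50%.

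This stands, and it removes any unconditional statement about the error. It does not rescue the plan, because the per-video reading still leaves videos nested in operators. A reader might equally infer that moving to videos restores 5%, but that holds only if there is no operator effect.

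It can also be said that a condensed article leaves the unit and the variance method to a fuller plan. That has some weight, and it lowers the severity. But the article is not silent here: it names the tests and describes the samples as independent.

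Two further inferences fail. The article plans no confidence intervals for frame-level accuracy, so it cannot be faulted for intervals that are too narrow. It also splits by patient and plans testing on unseen material, so overlap between these sets and the training data is not shown.

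**Conclusion.** The concern holds in conditional form. The article commits to independent-sample tests for a contrast between operators, without fixing the unit, allowing for clustering or choosing between the two tests. Independence is unsupported whether the frame or the video is the unit.

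The size rests on assumptions: about 7% to 45% for frames at ICC 0.01 to 0.30 and 20 frames per video, and about 7% to 21% for per-video summaries at operator ICC 0.05 to 0.10 and 5 to 15 videos per operator, against an assumed 5%. Which reading applies cannot be settled from the article.

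This should be fixed but is not critical, because the comparison as worded is not a listed primary or secondary outcome.

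**What to change.** Replace the sentence naming the two tests with a specification along these lines:

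1. **Unit.** The video is the observation. Name the per-video measure that decides (accuracy, recall, precision or F1).
2. **One analysis.** Use a single pre-named method that accounts for operator, such as a mixed model with experience as fixed effect and operator as random effect. If operators are few, use a comparison of operator means or a small-sample correction. Where a patient contributes more than one video, account for patient too.
3. **Reporting.** State the number of operators and videos per group, and give the difference with a 95% CI.
4. **Frame-level metrics.** If they are given intervals, use a bootstrap that resamples patients.
5. **No adjustment for incidence (apical or lateral) in the main comparison.** Under Ultrasound examination, the operator waits for a favourable incidence. Incidence may therefore be part of how experience affects the result, and adjusting could remove some of the difference under study.

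Naming the unit and the analysis needs no new data, but an operator code has to stay with each video; the article mentions only a patient code. The price is wider intervals and less apparent power, especially with few operators, and the comparison may then support only a descriptive conclusion.

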### Study design and setting

The study to be performed is a cross-sectional study divided into two separated parts (the training part of the machine learning approaches within the proposed framework and the testing phase on previously unseen frames and eventually on actual video scans) that will take place in two screening and referral prenatal diagnosis units: MEDGIN/GINECHO Clinic and University Emergency County Hospital Craiova (a tertiary maternity hospital).

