### Participants characteristics

We conducted a previous pilot study [36] during the development of this research question, where we noted a good acceptability of the method and most of the women had little difficulty deciding whether or not to have the scan protocol. This high acceptability was expected, as no supplementary US investigation was required.

All pregnant women in their first trimester are considered eligible for the study. They will be consecutively included in the study, depending on the availability of the US operators involved in this research. We will try to attract a large team of collaborators to investigate as many eligible cases as possible. The pregnancies with congenital heart disease will be excluded from the primary analysis.

Pregnant women will be admitted for their routine first trimester genetic and anomaly scan at 12-13 weeks of pregnancy. Gestational age will be determined based on the last menstrual period, confirmed with the first biometry dating scan.

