#### I. Data set

##### Ultrasound examination

Women recruited to participate in the study will undergo a fetal echocardiogram between 12-13+6 weeks of gestation. Appropriately competent practitioners will perform fetal scans. The ultrasound machines used are General Electrics

Voluson E10, E8 and E6, and Phillips Epiq Elite, with dedicated software for fetal heart assessment, equipped with convex transabdominal probes (frequency: 3-7MHz). Two-dimensional evaluation of each fetal heart includes a cine loop sweep obtained using Doppler or directional power Doppler techniques, from the four-chamber view plane by moving the transducer cranially towards the upper mediastinum, allowing the visualization of the following planes**:** four- chamber view, left and right ventricular outflow tracts, three vessels, and trachea view [37]. The acquisition time will be set for 5 seconds for each sweep. The cine loop sweeps will be stored on the hard drive of the ultrasound machine.

The protocols for the first trimester examinations are presented in Figs. 1 and 2. An apical-oblique lateral or lateral incidence from the right part of the thorax is considered optimal for visualization of the key-planes essential for fetal cardiac evaluation [29, 30]. Therefore, the operator will focus on other segments of fetal anatomy until the fetus reaches the optimal incidence; the angle beam is narrowed, and high-definition zoom is applied until only the thorax becomes visible, occupying approximately 80% of the screen. The operator then turned on the color flow gate, and a minimum of one duplex video file (grayscale and color / directional power Doppler) will be stored in each patient. The cardiac sweep is aimed to contain the key-planes of heart assessment described below and presented in Fig. 1.

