### Study limitations

A limited number of ultrasound devices types and techniques used to acquire the ultrasound sweeps may represent an impediment to large-scale implementation of the study results. The imaging of other ultrasound systems than the ones used to complete the study may differ significantly in the color format, and the performance of the software could be lower. We address this issue by using several color and directional power Doppler techniques and different generations of equipment in the study.

According to the study design, we will include in the study normal hearts; thus, the accuracy for detection of CHD cannot be evaluated from these data.

FE is feasible and efficient during the first trimester. Still, the continuous training process is impaired by the lack of specialists or their limited availability. Therefore, in our study design, the sonographer benefits from a second opinion provided by the developed software, which may be very helpful, especially if a more experienced colleague is unavailable. In addition, the software may be implemented on the ultrasound device so that the process could take place during the live examination.

Also, this software may help improve heart scanning skills because the operator will be stimulated to obtain satisfactory images regarding the key-planes of the cardiac sweep.

This study will provide insight into the feasibility of automatization of the 2D-FE. The aim is to provide a more early and accurate prenatal diagnosis of CHD to improve the treatment options for parents: pregnancy termination or birth in a specialized center. This will ultimately improve the couple’s satisfaction regarding the first-trimester anomaly scan performance, infant survival rates, and the quality of life of the newborns.

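### The expert-versus-novice video comparison uses unadjusted two-sample tests on non-randomised sets, so a difference in device or site mix would be read as an effect of operator experience.

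*Protocol article*

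**What the plan says.** The Statistical methods section of the protocol article sets up two groups of scans, "one containing video files made by experienced sonographers and the other made by inexperienced ones", and has experienced physicians validate the model's frame labels in both. It then names the analysis: "A t-test and a Mann-Whitney test for independent test samples will be used for verifying the differences in the results on the two sets". It mentions no covariate, stratum, matching factor or pairing.

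Other sections describe where the scans come from:

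- **Sites** (Study design and setting): "two screening and referral prenatal diagnosis units", one a clinic and the other a tertiary maternity hospital.
- **Machines** (Ultrasound examination): "Voluson E10, E8 and E6, and Phillips Epiq Elite, with dedicated software for fetal heart assessment", that is, four models from two manufacturers. Sweeps use either of two kinds of Doppler.
- **Inclusion** (Participants characteristics): women are "consecutively included in the study, depending on the availability of the US operators involved in this research".
- **Operators** (Interventions): women who meet the inclusion criteria are scanned by sonographers with three or more years of fetal cardiac imaging. How the inexperienced set will be obtained is not described.

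On equipment, the Study limitations section says that "other ultrasound systems than the ones used to complete the study may differ significantly in the color format", and that the software may then perform less well. Its answer is to use several Doppler techniques and several generations of machine. It does not mention balancing these between operator groups.

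**The concern.** The comparison is meant to show whether the model holds up when the person holding the probe is inexperienced. That reading needs the two sets to be alike in everything else that affects how well the model labels a frame. Nothing in the article makes them alike. Operators may work mainly at one unit and on one machine, so experience may travel with site and device.

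An unadjusted test then credits the whole difference to experience. If the novice videos came mostly from the less favourable machine, the tests could report a drop that experience did not cause. If they came mostly from the more favourable one, a real drop could be hidden. Running the t-test and the Mann-Whitney test side by side gives no protection, because both compare the same two unadjusted groups.

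This is the only planned test that addresses operator experience, and the system is intended for early-stage sonographers.

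**Working it through.** **Figures in the plan.** The article gives no sample size, effect size, SD or significance level for this comparison, so there is no figure to reproduce. The inputs below are assumptions chosen to show the mechanism.

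**Assumptions.** Two device groups; one performance value per patient; SD 10 points; device effect 5 or 10 points; 30 or 60 patients per set; no true effect of experience; two-sided 5% test.

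**Step 1: spurious difference.** Bias = device effect × (share of the better device in the expert set − its share in the novice set).

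- 10 × (0.80 − 0.40) = 4 points
- 5 × (0.80 − 0.40) = 2 points

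A 70% versus 30% mix gives the same 4 and 2 points. An equal mix gives 0.

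**Step 2: false-positive rate.** SE = √(2 × 10² / n); z = bias / SE; rejection ≈ Φ(z − 1.96) + Φ(−z − 1.96).

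- n = 60: SE = √(200/60) = 1.83
- n = 30: SE = √(200/30) = 2.58

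This takes 10 points as the total SD. The last column is a simulation of the t-test (4,000 replicates) with a 70/30 versus 30/70 mix and 10 points as the SD within a device.

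| Device effect | Per set | Bias | z | Formula | Simulation |
|---|---|---|---|---|---|
| 5 | 30 | 2 | 0.77 | 12% | 11% |
| 5 | 60 | 2 | 1.10 | 20% | 18% |
| 10 | 30 | 4 | 1.55 | 34% | 26% |
| 10 | 60 | 4 | 2.19 | 59% | 50% |

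If 10 points is the within-device SD in the formula as well, the 80/40 mix with a 10-point effect has variances 100 + 100 × 0.8 × 0.2 = 116 and 100 + 100 × 0.4 × 0.6 = 124. With n = 60, SE = √(240/60) = 2.0 and z = 2.0, so 59% becomes about 52%. With n = 30, 34% becomes about 29%.

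**Step 3: dependence on the imbalance.** For the same effects and set sizes, simulated t-test rates were:

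- equal mix: 2% to 5%
- 60/40 versus 40/60: 6% to 13%
- 80/20 versus 20/80: 19% to 87%

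The Mann-Whitney test stayed within about 3 points of the t-test throughout.

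**Step 4: effect of adjusting.** With a device term in a linear model, the false-positive rate for experience was 4.3% to 5.7% in every simulated scenario (30 to 150 per set).

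**Step 5: price of adjusting.** With a 70/30 versus 30/70 mix, the correlation between operator group and device is 0.70 − 0.30 = 0.40. For the same residual SD, the variance of the adjusted difference rises by 1/(1 − 0.40²) = 1.19, and its standard error by √1.19 = 1.09, or about 9%. If the mix were 100/0 versus 0/100 the correlation would be 1, and no model could separate the two.

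**The case against.** Several stronger readings are tempting, and the documents do not support them.

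- **That the protocol itself says device type changes performance.** A reader might infer this from Study limitations. The subject there is "other ultrasound systems than the ones used to complete the study may differ significantly in the color format", and lower performance is only a possibility. It is a caveat about generalising to outside machines. Extending it to the study's own four models is reasonable, but it is an inference.
- **That incidence decides the result.** The Ultrasound examination section says only that "An apical-oblique lateral or lateral incidence from the right part of the thorax is considered optimal". It also has the operator wait for a suitable position, standardises zoom and restricts gestational age, so part of this variation is controlled by design.
- **That the sets are known to come from different women, or known to be unbalanced.** The first is implied by independent samples but not stated. The second is possible but not shown; with an equal mix there is no device bias.

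It can also be argued that a condensed article may leave the make-up of the sets and any adjustment to an unseen document, and that the comparison is a robustness check and not a listed outcome. The second part limits the importance of the point. The first has some force, since an analysis plan could add adjustment. But the article does not leave the method open: it names two tests, and neither, as named, can adjust.

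A further objection concerns the remedy and stands in full. The incidence obtained is plausibly part of operator skill, so adjusting for it could remove part of the effect under study. Nor can regression rescue a design in which experience coincides with site or device.

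**Conclusion.** The point holds in limited form. The article fixes unadjusted independent-sample tests for two video sets, with no randomisation, pairing or balancing described, in a study with two units and four machine models. If device or site mix differs between the sets, the observed difference, or its absence, cannot be assigned to operator experience.

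Under the assumed inputs (device effect 5 to 10 points, 40-point difference in mix, SD 10, 30 to 60 per set), the false-positive rate is roughly 11% to 59%. It is at or below nominal when the mix is equal. None of these inputs is in the documents, so the range illustrates the risk and does not estimate what will happen in this study. The weakness should be corrected before the comparison is run. It does not show that the comparison is confounded.

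**What to change.** 1. Before anonymisation, store device, Doppler mode and site against the patient code that the Data preprocessing section already creates.
2. Where possible, select the expert and novice sets with a similar device and site mix. This comes first, because adjustment works only if the groups overlap.
3. Replace the two tests with one patient-level model of performance on operator group, adjusted for device and site. Where several operators contribute, add an operator term or use errors clustered by operator. Report the adjusted difference with a 95% CI.
4. Leave incidence out of the main model. Report it descriptively by operator group, or adjust for it in a sensitivity analysis only.
5. If experience turns out to coincide fully with site or device, state that the comparison cannot isolate experience.

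The cost is a few metadata fields, slightly more analysis work and a possible small loss of precision (about 9% on the standard error in the 70/30 example). No extra scans are needed.

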### Outcome measures

#### Primary outcome

The primary outcome of this study is an IS that can assist the early-stage sonographers in helping and training for accurate detection of the four first-trimester cardiac key-planes.

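### Two tests of difference cannot show that the model's performance is preserved on inexperienced sonographers' videos; an estimated difference with a confidence interval should be the main result

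*Protocol article*

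**What the plan says.** All of the following is in the protocol article.

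- **Purpose of the comparison** (Statistical methods; end of the sentence omitted): "The performance of the computational models on videos taken by inexperienced sonographers will be statistically assessed compared to the results on scans where an expert".
- **Material** (same section): "two sets of video scans will be completed, one containing video files made by experienced sonographers and the other made by inexperienced ones". No number of videos, operators or patients is given for either set.
- **How results are obtained** (same section; end of the sentence omitted): "The frames that the computational model labels will be extracted from the scans, and the experienced physicians will validate their predictions for both types of".
- **Analysis** (same section): "A t-test and a Mann-Whitney test for independent test samples will be used for verifying the differences in the results on the two sets". The text does not say which test decides, whether the frame or the video is the unit, or what will be concluded from either outcome. It mentions no interval and no tolerated loss.
- **Intended users** (Primary outcome): "an IS that can assist the early-stage sonographers in helping and training". The Aim section likewise presents the software as an aid for inexperienced or newly trained operators.
- **Who scans the enrolled women** (Interventions): trained sonographers with three or more years in fetal cardiac imaging.
- **The only stated size** (V. Sample size calculation) is for the whole data set, counted in images and videos: "it is intended to have at least 6000 images (around 1000 per class) within our data set, which could be extracted from approximately 300 ultrasound". Its basis is "A rule of thumb in deep learning is to have 1000 samples per class".

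**The concern.** The prospectively enrolled women are scanned by experienced operators, while the tool is meant for inexperienced ones. The comparison in Statistical methods is the only one the article states of the model's performance by operator experience. The useful answer is that performance on novice sweeps is not materially worse.

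A t-test or Mann-Whitney test does not address that question. A significant result says the sets differ, but not whether the loss matters. A non-significant result says only that no difference was found, and this becomes more likely as the sets get smaller or noisier. Without an interval or a tolerated loss beside the p-value, nothing in the stated analysis separates no relevant loss from too little information. At stake is a claim that the system works whatever the operator's experience, resting on a test that could not establish it.

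**Working it through.** **Plan's own figure.** There is none to reproduce. No alpha, power, effect size, SD, margin or set size is given for this comparison. The figures below are illustrations under stated assumptions.

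**Assumptions.** The video is the unit, the sets are of equal size, and tests are two-sided at 0.05. The set sizes of 15, 30, 64 and 150 are chosen to span a range and are not taken from the protocol.

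**1. Chance of missing a true drop of 0.5 SD (t-test).** With n videos per set, the non-centrality is 0.5 × √(n/2) on 2n − 2 degrees of freedom. The miss rate is 1 minus the power from the non-central t distribution.

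| n per set | non-centrality | critical t | power | missed |
|---|---|---|---|---|
| 15 | 1.37 | 2.05 | 0.26 | 74% |
| 30 | 1.94 | 2.00 | 0.48 | 52% |
| 64 | 2.83 | 1.98 | 0.80 | 20% |
| 150 | 4.33 | 1.97 | 0.99 | 1% |

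Simulated Mann-Whitney power (4,000 runs) is 0.23, 0.45 and 0.78 at 15, 30 and 64 per set, so it misses slightly more often: 77%, 55% and 22%.

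**2. The same on an accuracy scale.** Assume a true loss of 5 percentage points in per-video accuracy. The normal approximation uses 0.05 / (SD × √(2/n)) against 1.96. At SD 0.15 and n = 30 this is 0.05 / (0.15 × 0.258) = 1.29, which is missed 75% of the time.

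| n per set | SD 0.10 | SD 0.15 | SD 0.20 |
|---|---|---|---|
| 30 | 51% | 75% | 84% |
| 60 | 22% | 55% | 72% |
| 150 | 1% | 18% | 42% |

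Running both tests hardly helps. In simulation at SD 0.15 and a 5-point loss, at least one test was significant in 26% of runs at 30 per set and 47% at 60.

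**3. Why no set size cures it.** The 95% half-width in SD units is t × √(2/n).

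- At 30 per set it is 2.00 × 0.258 = 0.52. Even an observed difference of exactly zero would leave a 0.5-SD loss inside the interval.
- At 64 per set it is 0.35. An observed drop of 0.30 SD gives −0.65 to +0.05, which is not significant yet compatible with a drop of 0.65 SD.
- At 150 per set it is 0.23. An observed drop of 0.25 SD gives −0.48 to −0.02, which is significant yet excludes a drop of 0.5 SD.

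In each case the interval is informative and the p-value alone is not.

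**4. Unit.** The planned data set averages 6000 / 300 = 20 images per video. Treating frames as independent, 1200 per set would give a nominal 96% power for 90% versus 85%. That figure is not valid, because the protocol's own section II (Data preprocessing) reasons that one patient's images resemble each other more than those of different patients. It does show how far the result depends on the unstated unit.

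**The case against.** The strongest reply is that the article announces a search for differences and names standard tests for it. It makes no claim of equivalence or non-inferiority. It says nowhere that a non-significant result will count as equal performance, and nowhere that the sets are small. Margins and intervals are commonly left to an analysis plan, and the planned metrics will yield absolute performance on each set anyway.

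Much of this stands. A reader might infer that a small video set would pass as proof of equal performance. The documents do not support that, since they give neither a set size nor a decision rule. A reader might also take about 30 videos per set as the planned size, from 20% of 300 = 60 under the split in section II ("split into training, validation, and test sets, keeping the proportions of 60–20%-20"%). The protocol does not link the two video sets to that split, and a hold-out of scans by experienced operators would not supply the inexperienced half. The miss rates above run from 1% to 84% with the assumptions, so they do not locate the actual risk.

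The objection does not remove the choice of method. The tests are named in the article, not left open, and they cannot answer whether performance is preserved for the intended users. That holds whatever the set size and whatever the authors intend to conclude.

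**Conclusion.** The point holds in a limited form. The article fixes two tests of difference for the one comparison of model performance by operator experience. Those tests cannot demonstrate preserved performance, and a non-significant result could be misread as doing so. It is not established that such a misreading is planned or that a relevant loss is likely to be missed. The illustrated chance of missing a 0.5-SD drop falls from 74% at 15 videos per set to 1% at 150, and it assumes independent videos and equal sets. The change is worth making because it suits the question better at any set size and largely uses data already planned.

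**What to change.** Replace the two tests as the main result in Statistical methods with wording to this effect:

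*For each planned metric, the difference in per-video performance (inexperienced minus experienced) will be reported with a 95% confidence interval, with the video or the operator, not the frame, as the unit. Absolute performance on the inexperienced set will be given with its 95% interval. No material loss will be concluded only if the lower limit of the difference lies above a tolerated loss stated before the data are analysed. Otherwise the result will be called inconclusive or a loss, whatever the p-value.*

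The t-test or Mann-Whitney test may stay as a supporting result.

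Recall should be used only if experts also review the frames that the model does not label as key planes. The article describes validation of the frames the model labels. If that means key-plane labels only, missed planes go unseen, and precision or accuracy of the validated labels is the metric the data support.

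**Cost.** Mostly wording, plus one interval per metric. A tolerated loss has to be named and justified, recall may need extra annotation, and with few videos the result may be inconclusive. If the investigators also want to size the sets, n per set = 2 × (1.96 + 0.84)² × SD² / margin² for 80% power at a true difference of zero. This gives 63, 142 or 252 videos per set for a 5-point margin at SD 0.10, 0.15 or 0.20, and 16, 36 or 63 for a 10-point margin. These margins and SDs are assumptions for illustration, not recommendations.
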